**9PM – 2AM**

**MONDAY-FRIDAY**

**DAY 1:** 1/3 TESTED EVENING AFTER INTAKE DURING PHYSICAL EXAM

**5PM -9PM**

**TUESDAY-SATURDAY**

**DAY 7:** 1/3 TESTED 7 DAYS AFTER INTAKE NIGHT

**5PM -9PM**

**MONDAY-FRIDAY**

**PHYSICIAN’S ASSISTANT** OFFERS TO SWAB INMATE FOR HIV TESTING AS PART OF ROUTINE CARE

**RESEARCH STUDY STAFF** OFFERS TO SWAB INMATE FOR HIV TESTING AS PART OF ROUTINE CARE

**INTAKE NURSE** OFFERS TO SWAB INMATE FOR HIV TESTING AS PART OF ROUTINE CARE

DOES NOT CONSENT

CONSENTS

DOES NOT CONSENT

CONSENTS

CONSENTS

RESEARCH STUDY STAFF CONSENTS SUBJECT FOR STUDY AND HIV TEST

RESEARCH STUDY STAFF CONSENTS SUBJECT FOR STUDY AND HIV TEST

RESEARCH STUDY STAFF CONSENTS SUBJECT FOR STUDY AND HIV TEST

COMPETENT

INTERVIEWED, SWAB TESTED

NO INTERVIEW, NO SWAB TESTED

INTERVIEWED, SWAB TESTED

NO INTERVIEW, NO SWAB TESTED

INTERVIEWED, SWAB TESTED

INCOMPETENT

COMPETENT

INCOMPETENT

COMPETENT

INCOMPETENT

RESULTS GIVEN **SAME EVENING**

RESULTS GIVEN **SAME EVENING**

NOT INVITED BACK FOR TESTING

INVITED BACK FOR **DAY 7** TESTING

RESULTS GIVEN **NEXT** **MORNING**

RESEARCH STUDY STAFF PERFORMS COMPETENCY ASSESSMENT

RESEARCH STUDY STAFF PERFORMS COMPETENCY ASSESSMENT

RESEARCH STUDY STAFF PERFORMS COMPETENCY ASSESSMENT

DOES NOT CONSENT

NO INTERVIEW, NO SWAB TESTED

INVITED BACK FOR **DAY 1** TESTING

INMATE OPTS OUT

INMATE SWABBED

INMATE OPTS OUT

INMATE SWABBED

INMATE OPTS OUT

INMATE SWABBED

3.A.7 Analytic Plan

Ineligibility for routine HIV testing will be defined as those inmates who are medically incompetent using the MacArthur Competence Assessment Tool or who are otherwise found to be suicidal or in need of psychiatric holding by DOC staff. To address the first hypothesis, we will compare the proportion of individuals who are ineligible in each testing group using Mantel Haenszel testing. Because we anticipate that as many as 50% of jail detainees will be released within the first 72 hours, we will compare the proportion who accept testing in each group using Mantel Haenszel testing. Last, we will conduct multiple logistic regression of all intakes to assess the correlates of accepting mouth swabs as well as the correlates of accepting HIV testing. Secondary variables of interest will include demographic characteristics (it is possible, for example, that non-whites may be less likely to accept testing), drug use characteristics, presence of psychological distress, addiction severity scores, and history of past HIV testing. Data from this component of the study will be used to determine the effect size of a larger randomized controlled trial of routine HIV testing in jails.

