## Section IV: Research Plan

1. **Statement of Purpose:** What are the scientific aims of the study, or the hypotheses to be tested?

The aims of this study are:

1. To simulate and explore the feasibility of future implementation of a routine opt-out HIV testing protocol using rapid testing methods in the often-chaotic jail setting;
2. To determine the ability of subjects to pass a competency assessment in order to consent to routine HIV testing at varying times after entry into jail
3. To examine the acceptability among jail inmates of a routine HIV testing protocol using rapid HIV testing methods;
4. To evaluate the optimal time to perform routine HIV testing among inmates who are

competent to consent to testing, in a manner that not only maximizes public health but also attends to the safety and health status of individual inmates.

1. To assess the attitudes toward future widespread implementation of a routine rapid

HIV testing protocol by correctional, medical, and custodial staff

1. To assess the feasibility of implementing routine HIV testing in jails at different time points during and after entry processing from a systems operations perspective

Hypotheses:

1. A higher proportion of inmates approached for testing the night of intake will be

deemed incompetent to consent to testing (using the standardized MacArthur Competence Assessment Tool )compared to those inmates approached in the days after intake.

1. A higher proportion of inmates approached for testing the night of intake will present at

a higher risk for suicidal ideation and psychological distress (according to the nursing

staff’s mental health assessments and the standardized K6 psychological distress

scale) compared to those inmates approached in the days after intake.

1. A higher proportion of inmates approached for testing the night of intake will not

receive HIV testing (because they are either deemed incompetent or choose not to

provide consent for testing) compared to inmates approached on subsequent days.

1. A significant portion of individuals assigned to being approached for HIV testing on

Day 7 will leave the facility prior to Day 7 and will miss the opportunity to be tested.

1. Correctional medical and custodial staff will express resistance to implementing

widespread routine HIV testing in jail settings.

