None of the aforementioned studies adequately addresses the screening of inmates for psychological distress, intoxication, and withdrawal prior to conducting widespread HIV testing. A major challenge to implementing a routine HIV testing protocol in jails is determining the optimal time to test, taking into account an inmate’s ability to consent to testing and his or her level of psychological distress. Because the incarcerated experience high rates of suicidal behavior, mental illness, acute intoxication, and withdrawal, they might not be competent to consent to HIV testing or to receive a positive HIV test result, even though these same individuals might also be at highest risk for infection.1, 23 Therefore, when choosing the appropriate time to screen inmates for HIV, testing must be performed in a manner that not only maximizes public health, but also attends to the safety and health status of individual inmates. It is well documented that inmates are more likely to experience mental distress and present at a higher risk for committing suicide within the first 48 hours of incarceration.25, 26 A ten-year study of deaths in the Chicago Cook County jail found that suicides were the third leading cause of death among inmates, following heart and cerebrovascular disease.27 In addition, studies of jail populations at time of admission show that acute symptoms of serious mental illnesses requiring treatment are present in about 6% of males and 15% of females at booking.28, 29

Prisoners might be too distressed at their time of admission to consider the consequences of being HIV tested. In particular, distressed individuals might not be prepared to receive a positive HIV test result. Furthermore, recently incarcerated prisoners might be intoxicated or experiencing symptoms of withdrawal, thereby preventing them from providing informed consent. The challenge with postponing testing is that many individuals experience very short stays in jail, with about 1/3 leaving within 48 hours, followed by further attrition daily for the first week. Therefore, every day that testing is delayed a greater number of inmates will leave jail without being tested. Although several authors have acknowledged the importance of screening jail inmates for mental status and suicide risk before conducting widespread HIV testing, no literature exists evaluating the tradeoffs between early versus late testing with regard to individual health needs and public health benefit.

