5. At this point, on Day 0 and Day 1, the inmate will be given another opportunity to opt-out of consenting to participate in the study and to have the swab HIV tested. If the inmate opts out and is part of the Day 0 or Day 1 testing group, s/he will be invited back for testing on Day 1 or Day 7, respectively. If the inmate is part of the Day 7 testing group, s/he will not be approached again for testing.
6. If the inmate provides written consent, s/he will be administered the standardized MacArthur Competency Assessment Tool by a member of the study staff. The competency assessment tool will determine if the inmate understands the purpose of HIV testing and the potential benefits and risks or discomforts of choosing to test.
7. If the staff member deems the inmate competent according to the standardized tool, the inmate’s swab will be tested for HIV and the inmate will participate in an interview. The interview will include standardized instruments to assess opiate and alcohol withdrawal, psychological distress, and medical ability to consent to treatment. The schedule for administering the questionnaire is detailed in Table 1 below. The inmate’s swab will be tested immediately. Testing will be performed by the research study staff. Results will be recorded, and the swab will then be discarded in a hazardous waste container.
8. If the inmate is deemed not competent according to the standardized tool, further interviewing will be halted. The swab will be immediately discarded in a hazardous waste container and will not be tested. The inmate will be informed that even though s/he has consented to be HIV tested, the study staff does not believe that now is a good time for him or her to be HIV tested. If the inmate is part of the Day 0 or Day 1 testing group, the study staff will inform the inmate that he or she will be invited back for testing in the near future. Inmates in all three testing groups will also be informed that if this is not satisfactory, then they can always request an HIV test from the HIV testing counselors.
9. To explore feasibililty among correctional medical and custodial staff members, we will conduct one on one interviews with nurses, HIV counselors, mental health personnel, drug treatment staff, health services administrative staff members, and custodial staff to explore their attitudes about routine HIV testing. We will approach those staff members involved with intake procedures as well as medical staff.

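### Hypothesis 1 is about failing the MacArthur, but section 3.A.7 tests it on a composite that adds DOC suicidality and psychiatric holds, so a significant result would not show lower competence on intake night

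*Protocol*

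**What the plan says.** Protocol, Section IV, item 1 (Statement of Purpose). Hypothesis 1 predicts that intake-night inmates will more often be "deemed incompetent to consent to testing (using the standardized MacArthur Competence Assessment Tool )compared to those inmates approached in the days after intake". Aim 2 is likewise about passing a competency assessment at different times after entry. Hypothesis 2 is separate: it predicts more suicide risk and distress in the intake-night group, judged from nurses' mental health assessments and the K6.

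Protocol, section 3.A.7 (Analytic Plan). The definition of the analysis variable opens with the competence tool: "Ineligibility for routine HIV testing will be defined as those inmates who are medically incompetent using the MacArthur Competence Assessment Tool". It then widens the count by a second route that does not need the tool at all: "or who are otherwise found to be suicidal or in need of psychiatric holding by DOC staff". The next sentence ties this definition to the hypothesis: "To address the first hypothesis, we will compare the proportion of individuals who are ineligible in each testing group using Mantel Haenszel testing".

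Three other places bear on the point:
- Section IV, item 2 (Background) says that inmates "present at a higher risk for committing suicide within the first 48 hours of incarceration".
- Section 3.A.5.1, step 6, limits who is given the tool: "If the inmate provides written consent, s/he will be administered the standardized MacArthur Competency Assessment Tool".
- Section VI (Inclusion/Exclusion Criteria) decides eligibility from the MacArthur together with DOC clinicians' suicide watches and psychiatric holds. It says that the number incompetent will be counted, but that no other data on those inmates will be kept.

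**The concern.** The hypothesis names one endpoint and its test uses a wider one. The two are joined by an 'or', so any inmate with a DOC finding counts as a success for Hypothesis 1 whatever the MacArthur would have shown.

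This matters because the added component is not neutral with respect to timing. The Background and Hypothesis 2 both expect suicide risk and distress to be greater early in custody. If holds are more common on intake night, the composite will be higher there even if inmates are equally able to consent at all three time points. A reader would then take a difference in DOC holds for a difference in capacity to consent. Section 3.A.7 also says that the data will supply the effect size for a larger randomized trial, so a composite effect labelled as competence could be carried into that design.

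**Working it through.** **The plan's own figures.** The Protocol gives no figure for Hypothesis 1. Table 1 in section 3.A.4 concerns test uptake and is checked only to fix the design and test. With two-sided alpha 0.05, 80% power and two post-intake inmates per intake inmate:

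n = [1.96·√(1.5·p̄(1−p̄)) + 0.8416·√(p1(1−p1) + p2(1−p2)/2)]² / (p2−p1)², where p̄ = (p1+2·p2)/3.

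- Men, 60% v 76%: p̄ = 0.7067; (1.0929 + 0.4844)² / 0.0256 = 97.2, so 98. Table 1 has 98.
- Women, 75% v 88%: p̄ = 0.8367; (0.8874 + 0.4126)² / 0.0169 = 99.99, so 100. Table 1 has 100.

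All eight distinct rows reproduce. The design is therefore about 100 intake v 200 post-intake inmates per jail.

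**Inputs for the illustration (assumptions, since the documents give no rates for either component).**
- MacArthur failure m = 10% or 20%, the same in both groups, so Hypothesis 1 is false by construction.
- DOC suicidality or hold at intake h = 6% (men) or 15% (women). These are the Background's figures for acute serious mental illness at booking, used as a stand-in; they are not hold rates.
- Later holds: none, or half of h.
- Overlap: the two components independent, or half of held inmates also failing the MacArthur.
- Day 1 and Day 7 pooled, full numbers in each group, and both components known for everyone.

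**Formulas.** With k the later hold rate (0 or h/2):
- Independent: intake q0 = 1−(1−m)(1−h); later q1 = 1−(1−m)(1−k).
- Half overlap: q0 = m + h/2; q1 = m + k/2.
- P(reject) ≈ Φ{[(q0−q1) − 1.96·√(p̄(1−p̄)·0.015)] / √(q0(1−q0)/100 + q1(1−q1)/200)}, with p̄ = (q0+2·q1)/3 and 0.015 = 1/100 + 1/200. The small opposite tail is added.

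**One case in full.** Women, m = 10%, independent, no holds later: q0 = 0.235, q1 = 0.100, p̄ = 0.145. The numerator is 0.135 − 1.96·0.0431 = 0.0505 and the denominator is 0.0474. Φ(1.065) = 0.86; simulation gives 0.865.

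**Chance that the composite test rejects when competence does not differ (m = 10% / m = 20%).**

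| Overlap | Holds later | Men, h = 6% | Women, h = 15% |
|---|---|---|---|
| Independent | none | 29% / 17% | 87% / 63% |
| Independent | half | 11% / 8% | 30% / 20% |
| Half overlap | none | 13% / 10% | 46% / 32% |
| Half overlap | half | 7% / 6% | 15% / 11% |

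A test on MacArthur failure alone, simulated at the same sizes with equal failure rates, rejects in about 5%.

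**The case against.** The strongest reply is that the composite is the better measure of capacity. The Background describes incompetence as arising from intoxication, withdrawal, uncontrolled mental illness or severe distress, and Section VI uses the same two components to decide eligibility. The MacArthur reaches only inmates who accept the swab and sign consent, and suicidal inmates are excluded. If holds cluster at intake, the inmates least likely to pass leave the Day 0 assessed group, and a MacArthur-only comparison is biased towards no difference. This stands. It is a reason to state the denominator and keep the composite as a sensitivity analysis. It does not make the composite a test of a hypothesis worded on the MacArthur.

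It is also true that Section VI counts those incompetent, and that Section VIII (Structured Interviews) will examine competence frequencies over time. Neither is named as the test of Hypothesis 1.

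Three stronger readings are tempting, and the documents do not support them:
- A reader might infer that DOC findings accumulate over seven days in the Day 7 group and none in the Day 0 group. Section 3.A.7 defines ineligibility for testing, and Section VII speaks of incapacity for that day. Status at the scheduled approach is the natural reading.
- A reader might take the top of the table, 63% to 87% in women, as the expected error. It needs every hold to be gone by the next evening, independence of the two components, and a proxy rate that does not measure holds.
- A reader might say that the trial rests on this hypothesis. The primary outcome is the percentage who consent to and receive a test, and Table 1 is sized on that.

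**Conclusion.** The mismatch is explicit in the text: Hypothesis 1 is worded on the MacArthur, and section 3.A.7 tests it on MacArthur failure or a DOC finding. A significant composite would not show that inmates are less competent on intake night. The direction of the problem follows from the 'or' and from the Protocol's own expectation of higher early risk. Its size cannot be taken from the documents. Under the stated assumptions the rejection rate with equal competence runs from about 6%, hardly above nominal, to about 87%, and persistence and overlap of holds decide where in that range it falls. The point concerns a non-primary hypothesis in a pilot and leaves the uptake analysis untouched. It should be corrected because the correction is cheap and the results are meant to inform a larger trial.

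**What to change.** In section 3.A.7:

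1. Test Hypothesis 1 on MacArthur incompetence alone. State the denominator: inmates given the MacArthur at their assigned first approach, so that repeat approaches on Day 1 or Day 7 do not enter.
2. Report, by testing group and jail, how many were not assessed, separating refusal of the swab or consent from a DOC suicide watch or psychiatric hold.
3. Report DOC suicidality or hold status at the scheduled approach as its own outcome.
4. Keep composite ineligibility as a programme measure and as a sensitivity analysis for Hypothesis 1 in which held inmates are counted as not competent, with the components shown.

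The cost is a few sentences and one dating rule. No new data source is needed, since the composite already requires both components. However, Section VI keeps only a count of incompetent inmates, so counts must be tallied by reason, group and jail as they occur. The drawback is that the MacArthur-only comparison covers consenting, assessed inmates and may understate an intake-night deficit; the sensitivity analysis in item 4 is kept for that reason.

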**3. Research Plan:** Please provide an orderly scientific description of the study design and research procedures as they

directly affect the subjects.

3.A Prospective Pilot Routine Opt-Out Rapid HIV Testing Study

3.A.1 Overview: This pilot study proposes to perform routine opt-out testing as part of intake for approximately three hundred individuals at each study site (see below for description of study sites). Currently, both of the facilities where this study will be conducted perform voluntary HIV testing upon request. We will work closely with HIV testing counselors, correctional officers, and medical personnel involved with intake procedures in order to simulate as closely as possible future implementation of a routine testing protocol based on current CDC recommendations, using rapid HIV testing methods .

Our primary outcome is the percentage of subjects who consent to and receive an HIV test at a given time-point at each facility. This primary outcome will be assessed independently for each the male and female jails, since the relevant policy question is within each gender rather than between them i.e., policy-making is largely made independently for male and female jails. Additionally, women and men may have different attitudes and feelings toward HIV testing in general, toward HIV testing in jail, and are likely to present with different rates of mental illness, substance withdrawal, etc. that could potentially affect the primary outcome.30, 31

Intake procedures are conducted for new arrivals at each facility every Monday through Friday. Those arrested or booked on Friday evening, Saturday, or Sunday must wait in their local court holding facility until the following Monday night when they arrive at York C.I. (females) or New Haven Community Correctional Center (males). In addition, physical exams are conducted for all new arrivals the evening after they arrive at the facility, during second shift (3pm-11pm), i.e. every Tuesday through Saturday.

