For both jails, sample size calculations are made comparing the uptake at intake compared to subsequent timepoints. While, for the purposes of this pilot study, we do have three arms to have a more complete programmatic experience, the most relevant analysis is to just compare intake with post-intake. Since we are randomizing 1:1:1, this results in a 2:1 comparison for the primary outcome comparing the intake group with the collapsed post-intake groups. Table 1 provides sample size estimates for each arm, based on using the chi-square tests to compare the proportion uptake at each time-point within each jail setting and calculated using the standard sample size formula:

Where p is the proportion who receive an HIV test at intake, alpha is the type 1 error rate, beta is the type 2 error rate, and delta is the difference between the intake and post-intake groups. Plausible ranges of uptake rates are garnered from our current experiences in the jail system, through extensive clinical interviews and discussions with jail counselors. Only one other study has assessed routine testing in a jail setting. That study, however, is likely to have significantly higher uptake rates than will be seen in our study, since many of the subjects were repeat testers and the program had been running in that jail for some time.23

At our best-estimated initial uptake of 60% for men and 75% for women, 100 subjects in each arm will detect differences of 16% and 13%, respectively, with a type 1 error rate of 0.05 and power of 80%.

| **Table 1. Sample Size Calculations** | | |  |  |
| --- | --- | --- | --- | --- |
| **Jail Setting** | **Intake** | **Subsequent Time-points** | **N (each arm)** | **3N (Total Subjects)** |
| Men | 50% | 65% | 126 | 378 |
| 55% | 70% | 121 | 363 |
| **60%** | **76%** | **98** | **294** |
| 65% | 80% | 101 | 303 |
| 70% | 84% | 103 | 309 |
| Women | 65% | 80% | 101 | 303 |
| 70% | 84% | 103 | 309 |
| **75%** | **88%** | **100** | **300** |
| 80% | 92% | 93 | 279 |
| 85% | 95% | 99 | 297 |

3.A.5 Procedures

3.A.5.1 Testing

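### The Analytic Plan (3.A.7) compares three groups by Mantel-Haenszel, but the 80% power in 3.A.4 belongs to a two-group test within each jail; a three-group test has about 70-73%

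*Protocol*

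**What the plan says.** Three parts of the protocol bear on the primary test.

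- **Section 3.A.1 (Overview)** defines the primary outcome as the percentage who consent to and receive an HIV test, and adds: "This primary outcome will be assessed independently for each the male and female jails".
- **Section 3.A.4 (Sample Size Determination)** calls intake against post-intake the most relevant analysis. With 1:1:1 assignment, "this results in a 2:1 comparison for the primary outcome comparing the intake group with the collapsed post-intake groups". Table 1 is described as "based on using the chi-square tests to compare the proportion uptake at each time-point within each jail setting". At 100 per arm it claims detection of 16 points (men, from 60%) and 13 points (women, from 75%) "with a type 1 error rate of 0.05 and power of 80" percent.
- **Section 3.A.7 (Analytic Plan)** says of uptake: "we will compare the proportion who accept testing in each group using Mantel Haenszel testing". The groups are Day 0, Day 1 and Day 7. The section gives no collapsed contrast, strata, scores or degrees of freedom, and does not say that the test is run separately in each jail.

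**The concern.** The uptake sentence in 3.A.7 is the only between-group comparison of acceptance in that section, so it has to serve as the primary analysis. Read as written, it tests three groups. The power claim was worked out for two groups in a 1:2 ratio. A test that spreads its sensitivity over three groups detects the 3.A.4 alternative less often than a test aimed at it, so the 80% does not describe the analysis in 3.A.7.

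The name of the test adds a second ambiguity. Mantel-Haenszel testing usually implies strata, and 3.A.7 names none. A reader could take jail as the stratum, which would give one pooled result and conflict with 3.A.1.

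The power claim supports the enrolment of about 600 jail inmates, and the results are meant to supply the effect size for a larger randomized trial. The sample size and the analysis should refer to the same test.

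**Working it through.** **Inputs.** From 3.A.4: alpha 0.05, power 80%, base cases 60% v 76% (men) and 75% v 88% (women), 100 per arm, allocation 1:2 after collapsing. The text gives "alpha is the type 1 error rate, beta is the type 2 error rate" but no sidedness. Two-sided is assumed because one-sided gives 77 and 80 per arm, not the 98 and 100 in Table 1. Equal uptake on Day 1 and Day 7 is Table 1's own assumption.

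**Step 1: reproduce Table 1.** With p1 at intake, p2 post-intake and pooled p = (p1 + 2·p2)/3, the pooled-variance formula is

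n = [1.96·√(1.5·p(1−p)) + 0.8416·√(p1(1−p1) + p2(1−p2)/2)]² / (p2−p1)²

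- Men: p = 0.7067; (1.0929 + 0.4844)²/0.16² = 97.2, rounded up to 98. Table 1 has 98.
- Women: p = 0.8367; (0.8874 + 0.4126)²/0.13² = 99.99, rounded up to 100. Table 1 has 100.

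All ten rows reproduce exactly. Variants that fail for the two base cases (men/women): continuity-corrected 107/112, 1:1 allocation 133/139, unpooled variance 102/112. The 80% therefore belongs to the two-sided, two-group, 1:2 test.

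**Step 2: power of that test at 100 per arm.** Power = Φ{[(p2−p1) − 1.96·s0]/s1}, where s0 is the null and s1 the alternative standard error.

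- Men: (0.16 − 1.96·0.05576)/0.05755 = 0.881, power 81.1%.
- Women: (0.13 − 1.96·0.04528)/0.04902 = 0.842, power 80.0%.

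**Step 3: three-group association test (2 df) within a jail, same alternative.** Non-centrality λ = 100·[(p1−p)² + 2(p2−p)²]/[p(1−p)].

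- Men (60/76/76%): 1.7067/0.20729 = 8.23, power 73.1%.
- Women (75/88/88%): 1.1267/0.13666 = 8.24, power 73.1%.

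In 200,000 simulated trials the rejection rates were 72.3% and 71.3%. For 80% power this test would need about 117 to 118 per arm.

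**Step 4: one-df trend test within a jail, equally spaced scores 0, 1, 2.** With centred scores d, T = 100·Σd·p, V0 = p(1−p)·100·Σd², V1 = 100·Σd²·p(1−p) by group, and power = Φ[(T − 1.96√V0)/√V1].

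- Men: (16 − 1.96·6.439)/6.499 = 0.520, power 69.8%.
- Women: (13 − 1.96·5.228)/5.414 = 0.509, power 69.4%.

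Simulation gave 70.3% in both.

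| Test within one jail, 100 per arm | Men | Women |
|---|---|---|
| Intake v collapsed post-intake, 1 df (3.A.4) | 81.1% | 80.0% |
| Three groups, 2 df | 73.1% | 73.1% |
| Three groups, trend 0, 1, 2 | 69.8% | 69.4% |

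A Mantel-Haenszel test of the two collapsed groups within one jail is essentially the chi-square test and keeps about 80%. The loss comes from testing three groups, not from the name of the test.

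**The case against.** The strongest reply is that 3.A.4 already fixes the primary contrast by "comparing the intake group with the collapsed post-intake groups", and that strata, scores and test form are commonly left to a statistical analysis plan. On this view 3.A.7 is only loosely worded. Part of this stands. The absence of scores or degrees of freedom is not itself a fault. Because 3.A.4 names the most relevant comparison, the protocol does not support saying that the primary test is open to free choice after the data are seen. What remains is that 3.A.7 names a different comparison from 3.A.4. The wording of 3.A.4 does not settle this, since it speaks both of each time-point and of collapsed groups. Pilot status does not remove the mismatch, because the protocol makes a formal power claim.

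A reader might draw three stronger conclusions, which the protocol does not support:

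- **Power as low as 41-42%.** This needs a trend test scored by day (0, 1, 7), and the protocol states no such scores.
- **A pooled test across jails.** This would raise power (about 96% for the three-group 2-df test), but 3.A.7 does not name jail as a stratum and 3.A.1 excludes pooling for the primary outcome.
- **Monday intakes diluting the Day 0 group.** Weekend arrestees "must wait in their local court holding facility until the following Monday night", but the protocol counts time from jail entry, not arrest, and gives nothing from which to size such an effect.

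**Conclusion.** The mismatch is real and modest in size. The sample size calculation is sound for the test it describes. The analysis described in 3.A.7, taken as a three-group test within a jail, has about 73% power (2 df) or about 70% (equally spaced trend) against the stated 80%. That is a loss of roughly 7 to 11 percentage points.

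This rests on analysis within each jail as 3.A.1 requires, two-sided alpha 0.05, 100 per arm, Table 1's base-case rates, and equal uptake on Day 1 and Day 7. The last assumption is doubtful given the early release that 3.A.7 itself anticipates, but it is the one on which the plan's own figure depends.

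**What to change.** In 3.A.7, name the primary test as the two-sided, 1-df comparison of intake with the collapsed Day 1 and Day 7 groups, done separately in each jail. Use the chi-square test or its 1-df Mantel-Haenszel equivalent, and report a risk difference with a 95% confidence interval. Label any three-group or trend test secondary. In 3.A.4, remove the each-time-point wording so that both sections describe one test. This costs wording only: no added subjects, and Table 1 stands.

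If a three-group test is kept as primary, state its form and restate the power as about 70-73%, or re-power it (about 117 to 118 per arm for the 2-df test).

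Replacing the contrast with Day 0 against Day 1 alone is not a remedy for this point. At 100 v 100 it has 68.2% (men) and 66.0% (women) power, and would need 133 and 139 per arm for 80%.

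Optionally, stratify the 1-df Mantel-Haenszel test by intake night, since thirds are assigned within each night. This is a refinement, not the correction of an error. It has one condition: the Inclusion/Exclusion Criteria in Section VI keep only a count of inmates found incompetent to consent, so that count would have to be kept by night and testing group.
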